**Table 1 Tab1:**
[figure not shown]
Study schedule

*− t*_1_*:* Recruitment and information, *t*_0_: randomization,* t*_1_: postoperative period of 72 h in which the procedure with embolization of the MMA is performed or drug therapy with TXA is started, *t*_2_: follow-up 1 week postoperative,* t*_3_: follow-up: month postoperative (± 1 week), *t*_4_: follow-up: 2 months postoperative (± 1 week),* t*_5_: follow-up: 3 months postoperative (± 1 week) and close out

### Eligibility criteria {10}

#### Inclusion criteria

Patients who underwent surgery for unilateral CSDH for the first time no more than 24 h before inclusion in the studyAge ≥ 18 yearsWritten informed consent to participate in the study by the patient or a legal representative

#### Exclusion criteria

Conservatively treated CSDHAge ≤ 18 yearsBilateral CSDHPregnancy and breastfeedingRadiological evidence of an acute subdural hematoma, subarachnoid hemorrhage, epidural- or intracerebral hematomaStructural causes of subdural hemorrhages, e.g., arachnoid cysts, cortical vascular malformationsLack of inform consentInability to perform angiography/embolization within 72 h with simultaneous contraindications for taking tranexamic acid (inability to crossover)Previous history of burr hole trepanation, craniotomies, or craniectomies for other reasons

### Who will take informed consent? {26a}

Informed consent to participate in the trial will be obtained by the patients’ treating physician. Patients or their authorized surrogates will be given ample of time to ask questions and are requested to provide written informed consent within 24 h. The informed consent form will be signed by one of the researchers and the trial participant, or authorized surrogate if the trial participant has a decreased level of consciousness. In the latter case, informed consent will be obtained in the second instance if the trial participant becomes mentally competent during the study follow-up.

In the event of randomization to the control group, a specialist in neuroradiology will obtain separate informed consent about the embolization procedure.

### Additional consent provisions for collection and use of participant data and biological specimens {26b}

Together with informed consent for participation in the trial, additional consent is asked for reuse of the pseudonymised collected data for future research questions. For this study, no biological specimens will be collected.

## Interventions

### Explanation for the choice of comparators {6b}

Patients will be randomized into two groups, tranexamic acid vs. embolization with a 1:1 allocation after surgical relief of a chronic subdural hematoma. In the tranexamic acid group, postoperative adjuvant administration of 1500 mg tranexamic acid per day is performed over a period of 3 months; in the embolization group, embolization of the MMA on the affected side is performed 72 h postoperatively. The efficacy of both treatment methods in the adjuvant treatment of chronic subdural hematomas requiring surgery has been confirmed. However, there is no evidence-based, standardized postoperative treatment regime to reduce the incidence of recurrence in chronic subdural hematomas.

### Intervention description {11a}

Test group:

Patients who are randomized into the test group after verification of the inclusion criteria and consent for inclusion in the study will be treated adjuvantly after successful surgical relief (burr hole trepanation and/or any surgical technique) of CSDH within 48 h over a period of 3 months using a medication regimen of a total of 1500 mg tranexamic acid per day, divided into 2 or 3 daily doses, per os, over a period of 3 months.

The following contraindications to take this medication must be checked as part of the study inclusion:Hypersensitivity to the active substanceAcute thrombosis or thromboembolic diseases, such as deep vein thrombosis, pulmonary embolism and cerebral venous thrombosisCondition following a history of venous or arterial thrombosis.Hyperfibrinolytic conditions in the context of a consumption coagulopathySevere renal insufficiency/renal dysfunctionHistory of seizuresColor vision deficiencyMassive bleeding from the upper urinary tract (especially in hemophilia) [5]

(in the event of randomization into the test group with existing contraindications of taking tranexamic acid, *crossover into the control group* is possible).

2. Control group:

Patients who were randomized into the control group after checking the inclusion criteria and consenting to inclusion in the study after randomization are treated within 72 h postoperatively after successful surgical relief of the CSDH by means of endovascular embolization of the MMA on the affected side.

Embolization is performed using a microcatheter, which is inserted minimally invasive under sedation or intubation anesthesia via a transfemoral approach (alternatively also transradial) into the middle meningeal artery on the affected side. The target vessels are identified using digital subtraction angiography (DSA). This means increased radiation exposure for the patients assigned to the test group. The MMA originates in the infratemporal fossa from the maxillar artery, a branch of the external carotid artery. It enters the base of the skull through the foramen spinosum and gives off several branches to the dura mater from the point of entry. The middle meningeal artery can have different variations. Anastomoses with other branches of the external carotid artery and the internal carotid artery are possible. In particular, the variant in which the middle meningeal artery arises from the ophthalmic artery, which is probably more common than average in patients with CSDH, is an absolute contraindication for embolization, as there is an increased risk of central retinal artery occlusion with subsequent blindness [20]. In this case, crossover to the test group is possible.

The vasa nervorum of the facial nerve, the greater petrosal nerve and the trigeminal nerve usually originate from the middle meningeal artery shortly after passing through the foramen spinosum. Corresponding neurological deficits are therefore also possible here in the event of vascular occlusion. These anastomoses can usually be visualized well by angiography. To avoid complications due to incorrect embolization, care is taken not to embolize the proximal section of the middle meningeal artery [20].

A liquid embolizate like ONYX® or micro-electric coils can optionally be used to embolize the MMA.

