### Trial design {8}

TABASCO is an investigator-initiated, multi-center, randomized controlled trial testing whether postoperative treatment of chronic subdural hematomas using adjuvant drug therapy with tranexamic acid (test group) is equivalent to postoperative embolization of the MMA (control group) in terms of postoperative volume reduction of the hematoma and the need for revision surgery of CSDH within a follow-up period of 3 months. Eligible patients will be allocated in a 1:1 ratio to either the test or control group.

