### Sample size {14}

In order to estimate the required sample size, the volume change of a primary operated CSDH under the adjuvant therapy forms to be investigated is analogized with the recurrence rates of primary operated and adjuvant embolized or adjuvant drug-treated CSDH in the literature with regard to the target value defined within the primary objective. For example, the MEMBRANE study, which is currently being recruited, assumes a recurrence rate of 10% when combined surgical and interventional therapy is used [11]. In comparison, the work of Hibahashi et al. [27] puts the recurrence rate of CSDH treated with a combination of surgery and medication at around 2%. Based on this, using the *z*-test for independent samples and an error of the first kind (*α* = 0.05), a sample size of 276 patients (138 per group) is required to achieve a power > 0.8 to detect a difference of 8%.

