## Assignment of interventions: allocation

### Sequence generation {16a}, concealment mechanism {16b}, and implementation {16c}

After the neurosurgeon has checked the inclusion and exclusion criteria, the participants are assigned to treatment with tranexamic acid or embolization in a 1:1 ratio in each study center by means of block randomization after they have given their informed consent and the baseline data have been recorded.

If, in the course of the randomized group allocation, it will be apparent that there are exclusion criteria for inclusion in the test group in the sense of contraindications for the administration of tranexamic acid, or if it will be determine during the procedure that vascular anomalies prevent embolization in patients randomized to the control group, a crossover to the corresponding comparison group is possible after prior further clarification.

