### Trial status

This manuscript is based on trial protocol version 2.1, dated 25 April 2024. Recruitment at the leading center started on 01 May 2024. The patient recruitment has also started at a second study center. A further participating study center has recently been acquired. Recruitment has not started here. Several other potential study sites have been contacted. The end of the recruitment phase depends on the total number of participating study centers and is scheduled for the beginning of 2026 if a total of 5–8 sites are involved.

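### Patients who cannot take tranexamic acid can be randomized to it and then crossed over to embolization, which dilutes the comparison

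*Protocol article*

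**What the plan says.** Four places in the protocol article bear on this.

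- **Exclusion criteria (Eligibility criteria {10}).** The only feasibility exclusion is a joint one: embolization cannot be done within 72 h and, at the same time, TXA is contraindicated. The reason given in brackets is that the patient could not cross over. A TXA contraindication alone therefore does not exclude.
- **Intervention description {11a}, test group.** "The following contraindications to take this medication must be checked as part of the study inclusion". The list covers, among others, past thrombosis, severe renal impairment, past seizures and impaired color vision. Crossover to the control group is then permitted "in the event of randomization into the test group with existing contraindications of taking tranexamic acid".
- **Sequence generation {16a} and following.** Patients are allocated once the criteria have been checked and "after they have given their informed consent and the baseline data have been recorded". The crossover is described again, for cases where during allocation "it will be apparent that there are exclusion criteria for inclusion in the test group in the sense of contraindications" to TXA.
- **Intervention description {11a}, control group.** For an arterial variant that rules out embolization, "In this case, crossover to the test group is possible". This is found at angiography and is not contested here.

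The stated aim is to test whether TXA "is equivalent to postoperative embolization of the MMA (control group) in terms of postoperative volume reduction of the hematoma" and the need for revision surgery.

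**The concern.** A contraindication found at the inclusion check is known before allocation. Nothing in the eligibility criteria stops that patient from being randomized, and the intervention section provides for what happens if TXA is drawn. For such a patient the random draw does not decide the treatment.

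The consequence depends on the analysis:

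- **As randomized.** The comparison of assignments remains valid, but the contrast shrinks. That costs power in the difference tests planned under Statistical methods {20a}. Because the declared aim is equivalence, it also moves the result towards the hoped-for conclusion for a reason unrelated to the treatments.
- **As treated, or per protocol with switchers removed.** Contraindicated patients are found only in the embolization group, so the two groups are no longer comparable.
- **As randomized, restricted to patients without a contraindication.** This avoids both problems, but only if contraindication status was recorded before randomization in both arms. The check is listed under the test group, so recording it for embolization patients is not assured.

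By the wording of the joint exclusion, the mirror case is also open: a patient already known to be unsuitable for embolization within 72 h remains eligible if TXA is possible.

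**Working it through.** **Inputs from Sample size {14}.** Recurrence 10% with embolization and about 2% with TXA, α = 0.05, and "a sample size of 276 patients (138 per group) is required to achieve a power" above 0.8.

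**Assumptions.** The share *f* of patients with a TXA contraindication who can be embolized is not in the document; 5%, 10% and 20% are used. All of them switch, and they have the outcome of the treatment received.

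**Step 1: reproduce the plan's figure.** Two-sided z-test with pooled variance under the null, n = 138 per group:

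power = Φ[(Δ − 1.96·SE₀)/SE₁], where SE₀ = √[2p̄(1 − p̄)/n] and SE₁ = √[(p₁(1 − p₁) + p₂(1 − p₂))/n].

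With p₁ = 0.10, p₂ = 0.02 and p̄ = 0.06: SE₀ = 0.02859, SE₁ = 0.02818, and (0.08 − 0.05604)/0.02818 = 0.850, so power = 0.802. The 138 per group is the bare formula result, with no allowance for crossover.

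**Step 2: dilute the recurrence contrast.** The TXA-arm rate becomes 0.02(1 − f) + 0.10f = 0.02 + 0.08f, so the difference is 0.08(1 − f). For f = 10%, p₂ = 0.028, SE₀ = 0.02946, SE₁ = 0.02914, and (0.072 − 0.05775)/0.02914 = 0.489, so power = 0.688.

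**Step 3: dilute the volume contrast (primary outcome).** No standard deviation or target difference is given. The standardized difference that 138 per group detects with power 0.80 (two-sample t-test) is d = 0.3385. With switching it becomes d(1 − f).

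**Step 4: compare with leaving these patients out and not replacing them.** n = 138(1 − f) per group, at the full difference.

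| | f = 5% | f = 10% | f = 20% |
|---|---|---|---|
| Recurrence difference (points) | 7.6 | 7.2 | 6.4 |
| Recurrence power, enrolled and switched | 0.747 | 0.688 | 0.561 |
| Volume difference (SD) | 0.32 | 0.30 | 0.27 |
| Volume power, enrolled and switched | 0.759 | 0.713 | 0.611 |
| n per group if left out | 131 | 124 | 110 |
| Recurrence power, left out | 0.782 | 0.759 | 0.709 |
| Volume power, left out | 0.779 | 0.757 | 0.707 |

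Under full switching, leaving these patients out gives more power than enrolling them at every share.

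**Step 5: partial switching.** If only half switch and the rest behave as TXA patients, the diluting fraction is 2.5%, 5% or 10%. Recurrence power is then 0.776, 0.747 or 0.688, still slightly below the left-out figures. Volume power is 0.780, 0.759 or 0.713, about the same as leaving them out.

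**Step 6: composition if analyzed as treated.** The embolization group holds 138(1 + f) patients, of whom 2 × 138f are contraindicated, a share of 2f/(1 + f) = 9.5%, 18.2% or 33.3%. The TXA group holds none. If switchers are simply removed, the share in the embolization group is f, again against none.

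**The case against.** The strongest reply is that the allocation section describes contraindications that come to light during allocation, and that the word used in the intervention section can mean present at entry rather than known at entry. Enrollment takes place within 24 h of surgery, sometimes with surrogate consent, so a late discovery is plausible. This stands in part, and crossover should be kept for such cases. It does not remove the known case: the joint exclusion admits it, and the crossover wording in the intervention section is not limited to late findings.

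A second reply is that the same check cannot both be done before allocation and be uncertain for the embolization arm. If it is part of inclusion, everyone has it. That is fair as far as doing the check goes. What is not assured is that the result is recorded in both arms, and the restricted analysis depends on that record.

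Third, the size rests on an assumed share and on full switching, although crossover is only said to be possible. The recurrence figures concern the secondary outcome, and the volume effect is solved back from the sample size. All of this is true, and it limits the confidence in the size, though not the direction of the effect.

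Fourth, analysis populations may be set in a document not shown, and the article proposes no as-treated or per-protocol analysis. The bias described for those analyses is therefore conditional. The dilution under an as-randomized analysis is not cured by any choice of population unless status was recorded beforehand.

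Finally, these patients still inform the embolization complication outcome. That is correct; the loss concerns the comparison between treatments.

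**Conclusion.** The concern holds. As written, the protocol admits patients found at the inclusion check to be unable to take TXA, lets them be randomized to it, and then gives them embolization. They add nothing to the treatment contrast and pull the arms together.

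If 10% of patients are affected and all switch, power falls from 0.80 to 0.69 for recurrence and to 0.71 for volume; at 20% it falls to 0.56 and 0.61. At 5%, or with partial switching at 10%, the loss is modest, to about 0.75 or 0.76. The size depends on the assumed share, on the extent of switching, on switchers having the outcome of the treatment they receive and, for volume, on an effect chosen to give power 0.80. Confidence in the size is therefore medium. The change should be made because it is cheap, and because it also stops the assignment of a drug to patients for whom it is contraindicated.

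**What to change.** - **Eligibility {10}.** Make a TXA contraindication found at the inclusion check an exclusion on its own. Do the same for a known inability to embolize within 72 h.
- **Before randomization.** Complete and record the contraindication check in every patient, whichever arm follows.
- **Intervention description {11a} and allocation {16a–c}.** Delete the crossover for contraindications that already exist at inclusion. Keep crossover only for what is first discovered after randomization, such as a vascular anomaly at angiography or a contraindication that emerges late, and analyze the patient in the randomized arm.
- **Patients already enrolled.** If status was recorded before randomization in both arms, add an as-randomized analysis restricted to those without a contraindication. If it was not, do not reconstruct it afterwards, since the trial is unblinded; report crossovers by arm and reason beside the as-randomized result.

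**Cost.** One protocol amendment and one baseline case report form item, with no extra procedures. The change falls during recruitment: "Recruitment at the leading center started on 01 May 2024", and a second center is also enrolling. To randomize 276 patients, 276/(1 − f) otherwise eligible patients are needed, about 291, 307 or 345 at shares of 5%, 10% or 20%. The result will then apply to patients who can have either treatment, which is the population in which the question can be answered.

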### Criteria for discontinuing or modifying allocated interventions {11b}

Patients may withdraw their consent at any time without providing a reason and thus terminate their participation in the study prematurely. Withdrawal from the study and reasons, if known, will be documented. Study treatment stops if a surgical treatment for the CSDH is necessary during follow-up, in case of subsequent occurrence of an exclusion criterion or in occurrence of treatment-related complications during treatment. Crossover to the other study arm is not possible after the start of treatment in the respective study arm. Moreover, the principal investigator is entitled to terminate the study prematurely if new scientific findings in favor of one or the other treatment violate the equipoise principle.

### Strategies to improve adherence to interventions {11c}

Test group:

Treatment as part of the study takes place within 3 months of inclusion in the study. Follow-up visits will take place after 1, 4, 8, and 12 weeks. Upon enrollment in the study, the participant will receive instructions on how to take the medication, including when to take it, how to store it, the importance of taking the capsules as a whole and what to do in the event of a missed dose. The importance of adhering to the study protocol is also discussed.

At the follow-up visits, compliance with the treatment is monitored by asking whether the medication was taken regularly at the prescribed times, at what times the capsules were taken and whether the participant experienced any side effects. Study participants are asked to contact one of the researchers if they have any questions about the study medication during the treatment period. Medication monitoring will be performed by one of the researchers or by the research nurse who will also perform the follow-up measurements. The reason for any non-compliance will be recorded on the designated case report form.

2.Control group:

There is no possibility to influence patients’ adherence in that study group to the intervention. Embolization of the MMA constitutes the only study intervention, which is solely performed by the clinical investigators.

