**Fig. 2 Fig2:**
[figure not shown]
Preoperative volume measurement of a right-sided hemispheric chronic subdural hematoma using the CT data set

The following intervention-associated complications will be documented as part of the study:Vascular dissections caused by the guidewireDislocation of embolized materialIschemia caused by vascular occlusion during the interventionInflammation or abscesses at the puncture siteVascular fistula in the area of the puncture siteRetinal blindnessEpidural hematomas after perforation of the meningeal arteryAllergic reactions to the contrast mediumAcute renal failure

The following complications or adverse events associated with the use of tranexamic acid will be documented:Intolerance reactionsPulmonary embolismsVenous thrombosisEpileptic seizuresMyocardial infarctionsCerebral ischemic infarctionsAcute renal failure

All research data, including baseline data (NIHSS, mRS, hematoma volume, patient demographics and characteristics) prior to surgery, will be collected anonymously in an electronic data collection form at each study center. The PI of the trial summarizes these for all centers and exports data for statistical analysis. All investigators will be trained to perform outcome measurements and will be introduced to the data management prior to recruitment of the first patient.

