### Plans to promote participant retention and complete follow‐up {18b}

Participants will be informed about the study’s objective and relevance. The importance of completing the treatment and the follow-up evaluation, both for the study’s quality and for their personal chance to benefit from the therapy, will be emphasized. Participating patients are consciously informed that there are no personal benefits to take part in the study. Nevertheless, it is also explained that there is scientific evidence that patients who are treated as part of a clinical trial can obtain better results than patients who are treated under routine conditions.

Study follow-up is performed at 1 week and 1, 2, and 3 month (± 1 week) after evacuation of the hematoma with an outpatient clinic visit and CT or MRI scans. During these visits, all outcome measurements are performed by one of the researchers. To maximize participant retention, this study follow-up is parallel to the regular follow-up in the outpatient clinic (standard treatment). In addition, appointments for follow-up examinations are made as soon as the patient is discharged from inpatient treatment in order to increase compliance with participation.

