## Statistical methods

### Statistical methods for primary and secondary outcomes {20a}

The baseline data and outcome parameters are subjected to a simple descriptive data analysis (median, minimum, maximum and standard deviation in each case; mean only for metrically scaled characteristics).

For difference tests for nominal variables (gender, use of anticoagulation prior to surgery, occurrence of complications due to adjuvant therapy procedures, need for revision surgery), the Pearson chi-squared test is used.

For difference tests of ordinally scaled measured variables (NIHSS, mRS) within the respective groups at different points in time (linked samples), the data collected is tested for normal distribution using the Shapiro–Wilk test. In the case of a parametric distribution, the *t*-test is used for linked samples. In the case of a non-parametric distribution, the Wilcoxon test is used for connected samples (for two-group tests).

For the bivariate dependency analysis of the ordinal scaled characteristics between the two groups at the same point in time, the *t*-test for unconnected samples is used for a parametric distribution and the Mann–Whitney *U*-test for a non-parametric distribution after applying the Shapiro–Wilk test.

For metric variables (hematoma volume), which are subject to a normal distribution, the *t*-test for dependent samples is used to analyze the respective groups at different points in time. In the case of a non-parametric distribution, the Wilcox sign-rank test is used for the analysis.

For the bivariate dependency analysis of the metric characteristics between the two groups at the same point in time, after applying the Shapiro–Wilk test, the *t*-test for unrelated samples is used for a parametric distribution and the Mann–Whitney *U*-test for a non-parametric distribution.

In addition, a logistic regression is tested with the revision rate as the dependent variable and the treatment groups and baseline data as independent variables.

Furthermore, a correlation analysis of the relationship between the postoperative volume size and the revision rate as well as the postoperative neurological assessment and the revision rate is performed, in each case for mixed scaling pairs with the chi-squared test. The respective singular correlation analysis is followed by an analysis of the existence of a partial correlation between the two parameters in relation to the revision rate.

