### Adverse event reporting and harms {22}

Adverse events are defined as any undesirable experience occurring to a subject during the study, whether or not considered related to the investigational product (TXA) or investigational intervention (embolization). After participants have provided consent and been enrolled in the study, adverse events or complications of the treatment, will be documented and recorded until the end of the study period. Any serious adverse event that occurs in this trial will be reported to the principal investigator (PI). The PI must decide whether the participant can continue to participate in the study or whether he or she has to be excluded. The study team in every participating center will take responsibility for the treatment of the trails related adverse events or complications. The PI of the study will consider the continuation or discontinuation of the research under the following circumstances:◦ If a serious adverse event or disease report suggests that continuing the study poses safety concerns◦ If recruiting participants for the study becomes challenging, making it difficult to achieve the planned number of cases◦ When significant new information regarding the quality, safety, or efficacy of the medication (TXA) and interventional procedure (embolization) is obtained

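### The article states a side-effect question at follow-up visits for the tranexamic acid arm only, although complications are to be compared between the arms

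*Protocol article*

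**What the plan says.** All references are to the protocol article.

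- **Strategies to improve adherence {11c}, test group.** At the follow-up visits (1, 4, 8 and 12 weeks) patients are asked whether they took the medication regularly, "at what times the capsules were taken and whether the participant experienced any side effects". The person asking is a researcher or the research nurse who also takes the follow-up measurements.
- **Same section, control group.** "There is no possibility to influence patients’ adherence in that study group to the intervention". The paragraph adds that embolization is the only study intervention and mentions no question about symptoms or complications.
- **Adverse event reporting and harms {22}.** The definition of an adverse event is neutral as to arm and cause. After enrolment, "adverse events or complications of the treatment, will be documented and recorded until the end of the study period". No method of eliciting events is given for either arm.
- **Participant retention {18b}.** All participants have visits at 1 week and at 1, 2 and 3 months. "During these visits, all outcome measurements are performed by one of the researchers".
- **Outcome assessment {18a}.** The follow-up measurements named are NIHSS, mRS and hematoma volume. There is one list of complications for embolization ("The following intervention-associated complications will be documented as part of the study") and another for TXA ("The following complications or adverse events associated with the use of tranexamic acid will be documented").
- **Statistical methods {20a}.** Among the nominal variables to be tested for a difference are "occurrence of complications due to adjuvant therapy procedures, need for revision surgery), the Pearson chi-squared test is used".
- **Blinding {17a}.** Neither patients nor physicians are blinded.

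**The concern.** A patient who is asked about side effects reports more than one who is not, above all minor events after discharge. If one arm is asked at four visits and the other is not, the recorded rates differ even when the true rates are the same. Here the stated question falls in the TXA arm, so any distortion would raise the TXA rate relative to embolization. It could create an apparent excess on TXA or hide a true excess on embolization. Analysis cannot recover events that were never elicited.

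The complication rate is only a tertiary endpoint. However, the Discussion gives the risk-benefit comparison of the two adjuvant treatments as the reason a randomized trial is needed, so the safety comparison will be read closely.

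**Working it through.** **Step 1: what is equal between the arms and what is not.**

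| Element | TXA arm | Embolization arm |
|---|---|---|
| Visits at 1 week and 1, 2, 3 months {18b} | yes | yes |
| Outcomes measured by a researcher {18b} | yes | yes |
| Duty to record adverse events {22} | yes | yes |
| Stated question on side effects at visits {11c} | yes | none stated |
| Method of eliciting events in the harms section {22} | none stated | none stated |

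The visits and the duty to record are the same. The stated questioning is not.

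**Step 2: which events could be affected.** The embolization list has 9 items and the TXA list has 7. Most are diagnosed clinically, by angiography or by imaging: dissection, ischemia, fistula, epidural hematoma, pulmonary embolism, myocardial infarction and acute renal failure, for example. These depend little on a visit question. Intolerance reactions (TXA list) and mild inflammation at the puncture site (embolization list) depend on it more.

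**Step 3: reproduce the plan's sample size, which supplies n per arm.** The inputs from {14} are 10% versus 2%, alpha 0.05 and 138 per group. The article does not state whether the test is one- or two-sided; the two-sided pooled z-test without continuity correction reproduces 138.

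With d = |p1 − p2| and p̄ = (p1 + p2)/2:

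- SE0 = √(2p̄(1 − p̄)/n)
- SE1 = √((p1(1 − p1) + p2(1 − p2))/n)
- P(reject) = Φ((d − 1.96·SE0)/SE1) + Φ((−d − 1.96·SE0)/SE1)

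For 0.10 versus 0.02: SE0 = √(2 × 0.06 × 0.94/138) = 0.0286 and SE1 = √((0.09 + 0.0196)/138) = 0.0282. Then (0.08 − 0.0560)/0.0282 = 0.85, and the power is 0.802. The plan's figure of more than 0.8 is reproduced.

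**Step 4: illustration of unequal capture.** The article gives no complication or capture rates, so everything in this step is assumed. The true risk p of an event is the same in both arms. The TXA arm captures all events and the embolization arm captures a fraction s, so the observed rates are p and s·p. The sample is 138 per arm and the test is two-sided at 0.05.

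Worked case with p = 0.10 and s = 0.7: the observed rates are 0.10 and 0.07. SE0 = √(2 × 0.085 × 0.915/138) = 0.0336 and SE1 = √((0.09 + 0.0651)/138) = 0.0335. The first term is Φ((0.03 − 0.0658)/0.0335) = 0.143 and the second is 0.002, giving 0.145.

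Chance of a false significant difference (nominal 5%):

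| True risk p | s = 0.9 | s = 0.8 | s = 0.7 | s = 0.5 |
|---|---|---|---|---|
| 5% | 5.4% | 6.9% | 9.5% | 19.4% |
| 10% | 5.9% | 8.9% | 14.5% | 35.0% |
| 20% | 7.1% | 13.9% | 26.3% | 64.4% |

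With a capture gap of one tenth the effect is slight. The large figures need half of the embolization arm's events to be missed. For the mix of events on the two lists, that would be an extreme assumption.

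**The case against.** A reader might infer that embolization patients' events are collected only by spontaneous report, so that the chi-squared test sets solicited against unsolicited reports. The article does not say this. Embolization-arm reports are *not stated to be solicited*, which is a weaker statement. Complications of both treatments are tertiary outcomes, {18b} has researchers performing all outcome measurements at the same visits in both arms, and {22} applies to everyone. On a natural reading, a researcher may well ask embolization patients too.

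The side-effect question also sits in an adherence item, as part of compliance monitoring for a drug. A one-off procedure has no intake to monitor, so no counterpart would be expected there. And the article condenses a full protocol, which may hold the visit-level wording.

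Much of this stands. It rules out treating unequal collection as established, and it rules out reading the larger error rates above as expected values. The equal-risk assumption is also a simplification, because the two complication lists share only acute renal failure as an identically worded item. That difference in lists is a separate matter: a common list would not by itself make the questioning equal.

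What does not stand is that nothing needs changing. The article does not merely leave elicitation out; it specifies it for one arm. The person who asks also takes the follow-up measurements, so the answers reach someone who is collecting trial data. A site that follows the text literally would question one arm and not the other.

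**Conclusion.** The point holds as a minor one. The only active side-effect question that the article states is for the TXA arm, while complications are to be tested between arms in an unblinded trial. The asymmetry can raise the TXA rate relative to embolization, mainly for non-serious, patient-reported events. Serious and imaging-diagnosed events are little affected. Hematoma volume and revision surgery, the primary and secondary outcomes, are not affected.

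The size is unknown. If control-arm capture were 90%, the false-positive rate would be 5.4% to 7.1% for true risks of 5% to 20%; at 70% capture it would be 9.5% to 26.3%. These ranges rest on assumed risks and capture fractions, equal true risk in both arms and full capture on TXA. They show how sensitive the test would be to unequal capture; they do not show that it occurs.

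**What to change.** In Adverse event reporting and harms {22}, state that the same open, non-leading adverse-event question is asked in both arms at every follow-up visit (1 week and 1, 2 and 3 months) and recorded on the same form. Take the side-effect question out of the test-group paragraph in {11c}, and leave there only the questions on capsule intake.

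The cost is one sentence in the protocol and one common form. The visits already take place in both arms. The downside is that a few more minor events will be recorded in the embolization arm.
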